##### Physical functioning

The *Short Physical Performance Battery* (SPPB) [45] is a standardized instrument to test the lower extremity functionality (balance, gait speed, leg strength). Participants are required to show a stable stand in an upright position under three conditions (legs closed/feet together, semi-tandem stand, tandem stand). After that, comfortable gait speed will be assessed by measuring the time to walk a 4-m track, starting from a standing position and stopping when the first foot is past the 4-m line. Finally, a five times sit-to-stand transfer will be completed as fast as possible. Each domain is scored between 0 and 4 and SPPB overall scores range from 0 (low mobility/functionality) to 12 (full mobility/functionality). Clinically relevant improvements have been demonstrated to range between 0.99 and 1.34 points for the SPPB [45].

*Gait analysis* (GAITRite: CIR Systems Inc., Clifton, NJ, USA, Optogait: Microgate, Bolzano, Italy, MobilityLab: APDM Inc., Portland, USA, GaitUp: SA, Lausanne, Switzerland or Zebris PDM, Isny, Germany). Gait performance will be assessed by measuring step length, step width, gait speed, and double support phase on a 10-m track, using of one of the mentioned gait analysis systems. Each participant completes three trials: a test trial, one trial at preferred walking speed, and one trial at maximum walking speed. Measured data will be recorded and saved for later analysis by the gait systems software. An accompanying validation study will secure the comparability of the different gait measurement systems.

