##### Dual-task cognitive performance

The *Serial Sevens Test* (SST) [46] aims to assess cognitive functioning. During the SST, participants are being asked to count down from a certain number in steps of seven. Due to the poor cognitive functioning of most participants, a simpler version of the SST will be administered, in which participants have to count down in steps of 3 (S3T) and steps of 1 (S1T). The S3T and S1T will be tested during a single- and dual-task condition (i.e. during gait), in order to evaluate the cost of dual-tasking for cognitive functioning. The number of correct answers within 15 s will be recorded during single- and dual-task conditions as well as the gait parameters step length, step width, gait speed, and double support phase under dual-task conditions with a gait analysis system.

The *Verbal Fluency Test* (VFT) is an additional test for cognitive functioning and part of the MoCA [44]. The VFT is a phonemic fluency test, in which participants are asked to name as many words as possible in a certain time, starting with a specific letter (not allowed are names or numbers). It was shown that verbal fluency is reduced in elderly people with mild cognitive impairments as compared to their non-impaired peers [47]. In accordance to the S3T and S1T, the VFT will be administered during single- and dual-task conditions, to evaluate the cost of dual-tasking for cognitive functioning. The number of correct answers within 15 s will be recorded during single- and dual-task conditions as well as the gait parameters step length, step width, gait speed, and double support phase under dual-task conditions with a gait analysis system.

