### Data collection, management, and analysis

#### Statistical analysis

We will evaluate the effects of the intervention on every quantitative, qualitative, and ordinal outcome, using repeated measures or mixed models, “t” tests, Kruskall-Wallis Mann-Witney tests or the Chi-square tests, depending on the type of outcome and their normal or non-normal distribution. The primary analysis will be a mixed model between-group comparison of the SPPB, gait variables, Serial Sevens, and Verbal Fluency Test, utilising all available data points during follow-up. We will use the Bonferroni correction to appropriately adjust the overall level of significance for multiple comparisons. Between-group differences for all primary and secondary outcomes will be adjusted for baseline values, age, sex, and education. Secondary outcomes will be analysed with similar methodology, using repeated measures mixed model between-group comparisons. All statistical analyses will be performed using SPSS Statistics for Windows (version 25.0, IBM). Statistical significance level is set at *p* < 0.05.

Intention-to-treat analysis will be performed (participants who are randomized into groups after the collection of baseline data). For the intention-to-treat analysis, data of all trial patients in the groups to which they were randomized will be processed, regardless of whether they received or adhered to the allocated intervention. It is assumed that the majority of participants in the two arms will receive the appropriate number of intervention sessions. In addition, a per-protocol analysis of the participants who completed the study without major protocol violation (e.g., who attended more than 80% of the training sessions), will be performed. The per-protocol analysis will be performed as a secondary analysis, if there is a sufficient number of participants in the two arms, who do not receive the intervention protocol or are lost to outcome assessment. Data from those participants, who do not violate the treatment protocols, will be included in the per-protocol analysis. The multiple imputation (MI) technique will be used for dealing with missing data under the assumption that data are missing at random.

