#### Sample size estimate / power calculations

The required sample size was calculated with G*Power (Version 3.1.9.2, Heinrich Heine University of Duesseldorf) [62]. The sample size calculation was approximated with a 2 × 3-factorial analysis of variance (ANOVA) for repeated measures (within-between interaction, small effect size, power of .80 [1-β], 2-sided α-error (95% CI), 2 groups, 3 measurements) based on the primary outcome Short Physical Performance Battery (SPPB). The small effect size used for the calculation of required sample size is based on literature reviews and assumptions of clinically relevant changes for residents in nursing homes with probable cognitive impairment [63]. One hundred eight individuals per region are required in order to detect a clinically meaningful change of ≥1.0 point with a SD of 0.99 points. To account for potential dropouts before study completion, we will inflate the sample size by 30% (20% losses during follow-up; 10% mortality), resulting in a total sample size of 1120 individuals (140 per centre with 70 participants allocated to each group).

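### Single-step Bonferroni for the primary comparisons is valid, but Holm's step-down version gives the same error control and never rejects less: a cheap, low-severity improvement

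*Protocol article*

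**What the plan says.** The Statistical analysis section defines the primary analysis over several outcomes: "The primary analysis will be a mixed model between-group comparison of the SPPB, gait variables, Serial Sevens, and Verbal Fluency Test". The next sentence gives the multiplicity method: "We will use the Bonferroni correction to appropriately adjust the overall level of significance for multiple comparisons". The level follows a little later: "Statistical significance level is set at *p* < 0.05".

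The article does not say how many tests are in the family. Some of the named outcomes have several components. Under Physical functioning, "Gait performance will be assessed by measuring step length, step width, gait speed, and double support phase on a 10-m track", and this at preferred and at maximum speed. Under Dual-task cognitive performance, the number of correct answers is recorded "as well as the gait parameters step length, step width, gait speed, and double support phase under dual-task conditions".

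No step-down version, testing order, split of alpha or simultaneous confidence interval is mentioned. The sample size section is "based on the primary outcome Short Physical Performance Battery (SPPB") alone, with the settings "within-between interaction, small effect size, power of .80 [1-β], 2-sided α-error (95% CI), 2 groups, 3 measurements". It makes no allowance for multiple primary tests.

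**The concern.** Single-step Bonferroni tests every comparison at 0.05/m, including those that come after a clear success. Holm relaxes the threshold after each rejection without raising the overall error rate. The programme is meant to improve physical functioning and dual-task cognition together, and the difference between the two methods is largest when several effects are real. What is at stake is power for the second and later primary outcomes. A real effect on gait or dual-task performance could be reported as non-significant although the same data would support it at the same overall error rate.

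**Working it through.** **1. Inputs.** From the article: overall alpha 0.05; two-sided testing; power 0.80; 108 per region ("One hundred eight individuals per region are required in order to detect a clinically meaningful change of ≥1.0 point with a SD of 0.99 points"); eight regions. Assumed, because the article does not give them: m = 4 tests (one per named measure), correlation 0.3 between test statistics, and 80% power for each true effect at unadjusted 0.05. The plan states no figure for power after the correction, so there is none to reproduce.

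**2. Thresholds for m = 4.** Bonferroni uses 0.05/4 = 0.0125 for all four tests. Holm orders the p-values and compares them in turn with 0.05/4 = 0.0125, 0.05/3 = 0.0167, 0.05/2 = 0.025 and 0.05/1 = 0.05, and stops at the first failure. A p-value at or below 0.0125 passes at every step, so Holm rejects everything that Bonferroni rejects. This holds for any m.

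**3. Error control.** Suppose m0 of the m hypotheses are true nulls. When Holm first rejects a true null, it has so far rejected only false ones, at most m − m0 of them. The threshold in force is therefore at most 0.05/m0. The probability that any of the m0 true nulls has p ≤ 0.05/m0 is at most m0 × 0.05/m0 = 0.05, under any correlation. Bonferroni rests on the same inequality, so Holm adds no assumption.

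**4. Bonferroni power per true effect.** The test statistic has mean 1.960 + 0.842 = 2.802. The two-sided critical value at 0.0125 is 2.498. Power = Φ(2.802 − 2.498) = Φ(0.304) = 0.619, or 62%.

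**5. Holm power, by simulation** (equicorrelated normal statistics, 400,000 replicates per row, m = 4, correlation 0.3):

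| True effects | Base power | Bonferroni, per effect | Holm, per effect | Gain (points) |
|---|---|---|---|---|
| 1 of 4 | 80% | 62.0% | 62.1% | 0.1 |
| 2 of 4 | 80% | 61.9% | 64.3% | 2.4 |
| 3 of 4 | 80% | 62.0% | 67.4% | 5.4 |
| 4 of 4 | 80% | 62.0% | 71.7% | 9.7 |
| 4 of 4 | 99.9% | 99.5% | 99.9% | 0.4 |

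With all four effects real at 80% base power, the chance of showing all four is 25% with Bonferroni and 47% with Holm. The chance of at least one rejection is 93.0% with either, because the first threshold is the same. In no replicate did Bonferroni reject a hypothesis that Holm kept. The familywise error was 0.047 for both with no true effect. With one to three true effects it stayed below 0.05 for both (at most 0.036 for Bonferroni and 0.043 for Holm).

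**6. Why base power may be far above 80% for SPPB.** The 80% belongs to 108 per region. Pooled over eight regions that is 8 × 108 = 864 evaluable. Take f = 0.10 for the small effect (assumed), three measurements, independent participants and a repeated-measures ANOVA interaction with noncentrality λ = f² × N × 3/(1 − ρ). With within-person correlation ρ = 0, λ = 0.01 × 864 × 3 = 25.9; power is 99.7% at 0.05 and 98.8% at 0.0125. With ρ = 0.5, λ = 51.8 and both exceed 99.9%. The 108 itself does not follow from stated inputs (f = 0.10 with ρ = 0.5 gives 164; 108 needs ρ of about 0.67), but the comparison of Holm with Bonferroni does not depend on it.

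**The case against.** The strongest reply is that Bonferroni is a correct method, correctly stated. It controls the overall error, contradicts nothing in the article and creates no false-positive risk, so the point is one of efficiency only. That stands, and it sets the severity.

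The second reply is that the large gain is a best case, because it needs every primary effect to be real. The Background does not encourage that: it calls the nursing-home evidence on exercise unclear and inconsistent, and cites several studies with no cognitive benefit. This also stands. With a mix of real and null effects, the gain is a few points or less.

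The third reply is that Bonferroni has matching simultaneous confidence intervals and Holm has no simple ones. With Holm, an unadjusted 95% interval may exclude zero beside a non-significant adjusted p-value. A reader might therefore be tempted to say that power is given away for nothing, but something is traded. The reply has limited force here, because the article mentions no simultaneous intervals.

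A reader might also count a family of 27 tests: 4 gait parameters × 2 speeds = 8, 4 × 3 dual tasks = 12, 3 cognitive tests × 2 conditions = 6, and SPPB = 1. With all 27 effects real at 80% base power and correlation 0.3, power per outcome would be 38% with Bonferroni and 47% with Holm. The article does not say that each of these is a separate primary test, so the count is a construction and not a figure of the plan. That the correction covers the primary outcomes is itself inferred from the preceding sentence. Holm's advantage does not depend on either reading.

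**Conclusion.** The point holds as a cheap improvement of low severity. For any fixed family, Holm keeps the overall error at 0.05 under the same assumptions as Bonferroni and never rejects fewer hypotheses. Its benefit per true effect ranges from near zero to about 10 points under the assumptions of four tests, correlation 0.3 and 80% base power, and it depends mainly on how many effects are real. At very high base power it is about 0.5 points, so SPPB in the pooled sample may gain almost nothing. Any benefit would fall mainly on primary outcomes with weaker effects, whose power the article does not give.

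Two stronger readings are not supported. One is that the planned analysis is invalid; it is not. The other is that real effects would be missed only because of the procedure; even in the best case above, Holm still misses about 28% of true effects per outcome.

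**What to change.** In the Statistical analysis section, replace the Bonferroni correction with the Holm (step-down Bonferroni) procedure at an overall two-sided 0.05 for the primary between-group comparisons. Report Holm-adjusted p-values, and label the 95% confidence intervals as unadjusted.

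The cost is one sentence, settled before the unblinded analysis. It needs no new data or participants and no change of software, since Holm uses only the ordered p-values. The one loss is the simple matching simultaneous intervals. If the sponsor wants those, keeping Bonferroni is defensible and the plan should give that as the reason.

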#### Assignment of interventions

Assessment and data collection will be done by blinded assessors in a strictly pseudonymized form to guarantee a blinded data analysis.

To avoid performance bias, the measurements and the intervention follow a standardized protocol. All participant information and data will be stored securely and identified by a coded ID number only to maintain the participants’ confidentiality.

To avoid selection bias, a stratified randomization will be conducted to divide the participants into either an intervention group or a waiting time control group. The random allocation will be stratified and executed by lot by the director of the study who will receive the pseudonymized codes of the participants and their baseline characteristics and will not be involved in neither the assessment nor the intervention procedures. Stratification will be based on comparable sex, age, and cognitive performance (according to the Montreal Cognitive Assessment MoCA-Score [44]) to avoid differences in the baseline characteristics of the groups. After assigning the participants to either the intervention or waiting time control group, the pseudonymized participant codes will be sent to the study investigators who are responsible for the data management. The exercise scientist or physiotherapist, who will conduct the intervention, will receive only names of the participants in the intervention group and after 16 weeks names of the waiting time control group without being aware of the control group design.

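### The fixed covariate list omits MoCA, one of the three stratification factors, so tests may be slightly conservative; estimates stay unbiased

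*Protocol article*

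**What the plan says.** Under Assignment of interventions, the protocol article names three stratification factors: "Stratification will be based on comparable sex, age, and cognitive performance", with cognitive performance taken from the MoCA score. The stated purpose is "to avoid differences in the baseline characteristics of the groups".

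Under Statistical analysis, the main comparison is defined: "The primary analysis will be a mixed model between-group comparison of the SPPB, gait variables, Serial Sevens, and Verbal Fluency Test". The covariates are then fixed for every outcome: "Between-group differences for all primary and secondary outcomes will be adjusted for baseline values, age, sex, and education".

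Two of the three stratification factors are therefore in the model, and MoCA is not. No section adds it or explains its absence. Baseline MoCA enters only where MoCA is itself the (secondary) outcome, through the baseline value.

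**The concern.** When arms are balanced on a factor that predicts the outcome, chance imbalance in that factor no longer contributes to the sampling error of the treatment effect. A model without the factor still counts its variation as residual noise. The reported standard error is then larger than the true one, the interval is too wide, and the test rejects less often than its nominal level. Part of what the stratification bought is given away.

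The article gives some reason to expect MoCA to be prognostic for part of the primary set. The Verbal Fluency Test "is an additional test for cognitive functioning and part of the MoCA", the serial subtraction task was simplified because of the residents' poor cognition, and gait is also measured under dual-task conditions. The trial also applies a Bonferroni correction, so an already strict procedure would become stricter without need.

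**Working it through.** **Inputs.** From the article: stratification by sex, age and MoCA; covariates baseline value, age, sex and education; nominal two-sided level 0.05; power 0.80; 1120 residents planned, with a 30% allowance for loss. Not in the article: r, the partial correlation of MoCA with the outcome given the listed covariates. It is assumed here to lie between 0 and 0.5, with 0.1 to 0.3 as the main range. The article gives no figure of its own on this point to reproduce.

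**Formulas**, assuming MoCA is fully balanced by the stratification:

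- Reported standard error without MoCA, relative to with MoCA: 1/√(1 − r²).
- Effective critical value: c = 1.96/√(1 − r²).
- Actual type I error at nominal 5%: 2 × (1 − Φ(c)).
- Power, where the model with MoCA has 80%: Φ(2.8016 − c), with 2.8016 = 1.96 + 0.8416.
- Sample factor that restores 80%: ((c + 0.8416)/2.8016)².

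**Worked case, r = 0.3.** 1 − 0.09 = 0.91, and 1/√0.91 = 1.048. c = 1.96 × 1.048 = 2.055. Type I error is 2 × (1 − Φ(2.055)) = 4.0%. Power is Φ(2.8016 − 2.055) = 77.2%. The sample factor is (2.897/2.802)² = 1.07.

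| Assumed r | Interval wider by | Type I error | Power | Sample equivalent |
|---|---|---|---|---|
| 0 | 0% | 5.0% | 80.0% | 0% |
| 0.1 | 0.5% | 4.9% | 79.7% | 0.7% |
| 0.2 | 2.1% | 4.5% | 78.8% | 2.9% |
| 0.3 | 4.8% | 4.0% | 77.2% | 6.9% |
| 0.4 | 9.1% | 3.2% | 74.6% | 13% |
| 0.5 | 15.5% | 2.4% | 70.5% | 23% |

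The table uses the unadjusted 5% level. Under a Bonferroni-adjusted level the interval ratio is the same. The power loss is somewhat larger, because the gap c − c√(1 − r²) grows with the critical value.

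**Simulation check.** Allocation was stratified by MoCA (four levels), age and sex, with 1120 × 0.7 = 784 residents analysed and 3000 runs per r. Education and clustering were not simulated.

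- At r = 0.3 the true standard error was 0.0666 without MoCA and 0.0664 with it, while the reported one was 0.0714 against 0.0682 (ratio 1.048).
- At r = 0.5 the true values were 0.0627 and 0.0616, and the reported ones 0.0715 and 0.0619 (ratio 1.155).
- Rejection rates under no effect, without MoCA, were 5.4%, 4.6%, 4.9%, 3.7%, 4.3% and 2.6% for r = 0 to 0.5. With MoCA they were 5.4%, 4.6%, 5.5%, 4.4%, 5.7% and 5.6%. Simulation error is about √(0.05 × 0.95/3000) = 0.4 percentage points, so these rates confirm the direction rather than the exact values. The ratios of reported standard errors match the formula closely.

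**The case against.** Four points can be made for the plan as it stands.

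*The loss is probably small.* What matters is the partial correlation after the outcome's own baseline value, age, sex and education. That baseline value will carry much of what MoCA knows, most clearly for Verbal Fluency. The sample size rests on SPPB, a physical measure, and nothing in the article shows that MoCA predicts SPPB beyond baseline SPPB. This stands, and it is why the range starts at no loss.

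*The degree of balance is not known.* Allocation is by lot, and the article gives no MoCA cut-points. How closely MoCA is balanced, and hence how far the standard error is overstated, cannot be read from the text. This stands too. The table describes full balance and all else fixed.

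*An article condenses a longer plan.* This is weak here, because the covariate list is stated outright for all outcomes and not left to another document.

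*Baseline values might be meant to include MoCA.* The natural reading is each outcome's own baseline. If the sponsor meant more, one clarifying phrase settles it.

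On size, a reader might infer that adding MoCA at r = 0.3 is worth about 10% more residents, since 1/0.91 = 1.10. That figure belongs to a trial that does not balance MoCA, where adjustment reduces the real sampling variance. Here the stratification has already removed nearly all of that variance, and what remains is an overstated reported error. The equivalent is then about 7% at r = 0.3, 3% at r = 0.2 and under 1% at r = 0.1.

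**Conclusion.** The mismatch between the stratification factors and the covariate list is certain from the text. Its consequence is a modest loss of efficiency. For r between 0.1 and 0.3, intervals are about 0.5% to 5% wider than needed and power falls from 80% to between 79.7% and 77.2%. This rests on an assumed r and on MoCA being well balanced by the stratification. Serial subtraction, Verbal Fluency and dual-task gait are the likeliest to be affected. MoCA as an outcome is not affected at all.

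Two stronger readings are not supported. A reader might infer that an analysis which does not follow the randomisation is invalid, but leaving out a balanced factor neither biases the estimate nor raises the type I error, and the planned tests err on the cautious side. A reader might also take the inclusion of education, which is not a stratification factor, as part of the fault. Adjusting for a covariate named in advance is legitimate and needs no change.

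**What to change.** In the Statistical analysis section, add baseline MoCA to the covariates of the between-group models for all primary and secondary outcomes other than MoCA itself. Use either the continuous score or the strata as applied at randomisation, and name the choice in advance. Keep baseline value, age, sex and education. The model for MoCA as an outcome needs no addition, because its baseline value is already there and a second copy would duplicate a term.

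The cost is one covariate (or a few stratum terms), which is trivial with 1120 residents planned. No new data are needed, since MoCA must be measured before allocation for the stratification. Making the change before the allocation is unblinded avoids any later dispute over a covariate chosen after seeing results.

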**Methods:**

A two-arm single-blinded multicenter randomized controlled trial will be conducted, including 48 nursing homes in eight regions of Germany with an estimated sample size of 1120 individuals. Participants will be randomly assigned to either a training or a waiting time control group. For a period of 16 weeks the training group will meet twice a week for group-based sessions (45–60 min each), which will contain exercises to improve physical functioning (strength, endurance, balance, flexibility) and cognitive-motor skills (dual-task). The intervention is organized as a progressive challenge which is successively adapted to the residents’ capacities. Physical functioning, cognitive performance, and quality of life will be assessed in both study groups at baseline (pre-test), after 16-weeks (post-treatment), and after 32-weeks (retention test, intervention group only).

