### Intervention

The exercise program consists of 32 sessions for a period of 16 weeks. One training session has a duration of 45–60 min and takes place twice a week. Exercise sessions will be administered by at least one certified exercise scientist or physiotherapist with group sizes ranging from four to 15 participants. The program follows IAGG guidelines and combines previously published exercises that have proven to be beneficial for cognitive-motor performance in older people in the community and in need of care [7, 8, 12, 20, 35, 56–59]. Training focusses on daily situations which are commonly associated with an increased fall risk and it mostly includes challenging walking exercises (e.g., brisk walking, starting, stopping, avoiding obstacles, turns). During these exercises, participants are also exposed to a variety of cognitive tasks under single- and dual-task conditions, designed to challenge their focus of attention with acoustic and visual stimuli and specific executive functions. Furthermore, exercises for strength, balance and flexibility as well as endurance performance associated with walking are integrated.

To ensure a controllable structure, training sessions are divided in five parts: 1. 5–10 min mobilisation and warm-up (e.g., range of motion exercises for the wrists, hip, shoulders, knees, and ankles). 2. 10 min coordination, balance, and cognitive exercises (e.g., standing balance, bodyweight shifting, motivational cognitive-motor games with group interaction including balls and scarfs). 3. 20 min aerobic walking exercises (e.g., under different single and dual-task conditions). 4. 10 min strength exercises (e.g., chair rises, upper body and trunk exercises with additional materials and weights, functional lower-limb exercises). 5. 5–10 min calm down (e.g., stretching and relaxing exercises).

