Discontinuation of the intervention may occur in case of health decline or if a participant wishes to stop taking part in the group intervention. To improve adherence and to promote retention, the therapists will give explanations about the purpose of the intervention and the possible benefits of the exercises. Attendance of each participant will be recorded and reasons for drop outs will be documented. No other concomitant group exercise interventions are permitted besides usual care and physiotherapy. Control group participants will be asked to continue their regular everyday activities.

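### At week 16 the 80% attendance criterion for the per-protocol analysis can select only the intervention arm, because waiting-list controls have been offered no sessions by then

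*Protocol article*

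**What the plan says.** The Statistical analysis section of the protocol article makes intention-to-treat the main approach and adds "a per-protocol analysis of the participants who completed the study without major protocol violation (e.g., who attended more than 80% of the training sessions"). It then states the inclusion rule: "Data from those participants, who do not violate the treatment protocols, will be included in the per-protocol analysis". The same paragraph assumes that "the majority of participants in the two arms will receive the appropriate number of intervention sessions".

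Other sections describe when sessions happen and to whom:

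- Intervention: "The exercise program consists of 32 sessions for a period of 16 weeks". For the other arm: "Control group participants will be asked to continue their regular everyday activities".
- Assignment of interventions: randomisation will "divide the participants into either an intervention group or a waiting time control group". The trainer receives the intervention-group names at the start and "after 16 weeks names of the waiting time control group without being aware of the control group design".
- Abstract, Methods: outcomes are measured at baseline, "after 16-weeks (post-treatment), and after 32-weeks (retention test, intervention group only"). The Trial design section says the same of T3.
- Intervention, on discontinuation: a resident may stop because of worsening health or by choice. Attendance is recorded, and other group exercise programmes are not allowed.

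**The concern.** A per-protocol comparison is open to bias when its membership rule depends on something that happens after randomisation and operates differently in the two arms. Here the one criterion the article offers as an example is attendance, and one arm has nothing to attend before the outcome is measured. Residents whose health worsens, or who lose interest, can fail the criterion in the exercise arm. Comparable residents in the control arm cannot. If attendance is related to how a resident fares over the 16 weeks, the two per-protocol groups differ in prognosis even when training does nothing, and the difference favours the intervention. Adjustment for baseline value, age, sex and education cannot fully remove this, because deterioration during weeks 1–16 comes after baseline.

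**Working it through.** **Step 1: where the rule can act.**

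| Point | Intervention arm | Control arm | Source |
|---|---|---|---|
| Sessions offered before T2 (week 16) | 32 | 0 | Intervention; Assignment of interventions |
| Measured at T2 | yes | yes | Abstract, Methods; Trial design |
| Measured at T3 (week 32) | yes | no | Abstract, Methods; Trial design |
| Completion rule | applies | applies | Statistical analysis |
| Ban on other group exercise | applies | applies | Intervention |
| More than 80% of sessions | applies | cannot apply | Statistical analysis |

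0.8 × 32 = 25.6, so the criterion means at least 26 of 32 sessions. T2 is the only post-baseline time point with both arms, so it carries the only between-group comparison. A control has attended none of zero sessions by then, and the criterion cannot separate one control from another. Using controls' attendance in their own later course would not help, because it would select them on behaviour that follows their T2 outcome.

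**Step 2: illustrative size under no true effect.** The protocol gives no figure to reproduce here.

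- From the Sample size section: SPPB SD 0.99; target 1.0 point; 1120 residents, so 560 per arm; 30% loss, so 560 × 0.7 = 392 completers per arm.
- Assumed, not in the documents: share q of the intervention arm passing, 0.5 to 0.8; correlation r of latent attendance with the T2 change after adjustment, 0.1 to 0.3; normality.

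If the top share q is kept, the cut-off is c = z(1−q), and the mean latent attendance of those kept is m = φ(c)/q. For q = 0.5, 0.6, 0.7, 0.8 this gives m = 0.798, 0.644, 0.497, 0.350. The spurious difference is r × m × 0.99 points:

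| r | q = 0.5 | q = 0.6 | q = 0.7 | q = 0.8 |
|---|---|---|---|---|
| 0.1 | 0.079 | 0.064 | 0.049 | 0.035 |
| 0.2 | 0.158 | 0.127 | 0.098 | 0.069 |
| 0.3 | 0.237 | 0.191 | 0.148 | 0.104 |

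**Step 3: false-positive rate at nominal two-sided 0.05.** In SD units the bias is b = r × m. The variance among those kept is v = 1 − r² × m × (m − c). The standard error is SE = √(v/(392q) + 1/392), and k = b/SE. The rate is 1 − Φ(1.96 − k) + Φ(−1.96 − k).

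Example, r = 0.1 and q = 0.5: b = 0.0798, v = 0.9936, SE = √(0.9936/196 + 1/392) = 0.0873, k = 0.914, rate 0.15.

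| r | q = 0.5 | q = 0.6 | q = 0.7 | q = 0.8 |
|---|---|---|---|---|
| 0.1 | 0.15 | 0.12 | 0.10 | 0.08 |
| 0.2 | 0.45 | 0.35 | 0.25 | 0.15 |
| 0.3 | 0.80 | 0.66 | 0.48 | 0.29 |

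Steps 2 and 3 treat the 392 controls as unselected on attendance, and residents as independent. They ignore clustering by home and the planned Bonferroni correction.

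**The case against.** A reader might infer that the analysis sets selected adherers against all controls, and that frail residents leave one arm only. The text does not support that. The per-protocol set requires study completion and no major violation, without limit to one arm. Controls who die, are lost or join other group exercise would also be excluded, and the sickest residents fail the completion rule in both arms. What remains is the extra selection on attendance among completers.

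The 80% figure is introduced as an example, and a condensed article may leave the full list of violations, including those for controls, to a fuller plan. This stands as a reason not to treat the example as the whole definition. It does not remove the asymmetry of the one criterion stated, nor the conflict between the sentence on both arms and the waiting-list design.

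The analysis is secondary, and no decision rule depends on it. A reader might expect it to be presented as confirmation of efficacy, but the article does not say so.

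The size rests on assumed values. Baseline adjustment may leave only a weak residual correlation. Control completers are themselves partly selected on health, so the net bias could be smaller than shown. The article gives no number for its small effect size. Its one numeric target is 1.0 point with SD 0.99, and the illustrated bias is at most about a quarter of that. These limits stand.

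**Conclusion.** The point holds for the secondary per-protocol analysis and does not touch the intention-to-treat result. Two things follow from the text alone: the attendance criterion can select only the intervention arm in the sole between-group comparison, and the sentence on sessions in both arms contradicts the design. That the bias runs towards benefit is probable rather than established; it follows if missed sessions reflect poorer health or lower motivation, as the stated reasons for stopping suggest.

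On the assumed inputs the spurious difference is about 0.04–0.24 SPPB points. This would not by itself imitate the 1.0-point target. At the planned sample size it would still raise the false-positive rate above the nominal 5%: from about 0.08 at the weakest correlation and highest pass rate to 0.80 at the strongest correlation and lowest pass rate. The change is worth making because it is cheap, not because the main conclusion is at risk.

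**What to change.** 1. Correct the sentence on both arms so that it says only the intervention arm is offered sessions before T2.
2. Replace the attendance-filtered comparison as the adherence analysis with an instrumental-variable analysis (for example two-stage least squares) of all randomised residents. Use randomised arm as the instrument and the intention-to-treat covariates, and handle missing T2 outcomes by the multiple imputation already planned. Choose the exposure in advance:
   - attendance above 80% (yes/no), which gives a complier effect; or
   - number of sessions attended, 0 for controls to week 16, which gives an average effect per session under linearity. This is not a complier effect and should not be labelled as one.
3. If the filtered comparison is kept, label it descriptive and do not offer it as support for efficacy.

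The cost is analysis wording only, since attendance is already to be recorded. The price is a wider interval and the exclusion restriction, under which allocation affects the outcome only through the chosen exposure. With the yes/no version this means that attendance below the threshold has no effect. The per-session version adds linearity. Since controls have zero exposure, the estimate essentially rescales the intention-to-treat effect, so it gives no independent test of the null.
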